**Fig. 1 Fig1:**
[figure not shown]
Schematic representation of Task 1. **Abbreviations**: [18 F]-FDG-PET/CT: [18 F]Fluorodeoxyglucose positron emission tomography, ADL: Activities of Daily Living, C.E. CT: contrast-enhanced computed tomography, IADL: Instrumental Activities of Daily Living, MDASI: MD Anderson Symptom Inventory, SBRT: Stereotactic Body Radiotherapy

Main tumor characteristics including overall staging and lesion location will be collected, as well. This qualitative information will be complemented by the inclusion of qualitative and semiquantitative parameters Task 2. Finally, treatment characteristics will be retrieved for both treatment cohorts. In the case of SBRT, beyond the prescribed total dose, clinically meaningful dose-volume statistics will be considered (i.e. maximum dose, minimum dose, mean dose, and percentage volume receiving greater than or equal to the prescription dose). Alongside punctual dose parameters, the area under the dose-volume histogram curve will also be evaluated to better assess dose distribution to both the target volume and to the nearby healthy structures.

### Treatment modalities

Following multidisciplinary discussion within the institutional lung tumor board, either SBRT or surgery will be indicated [18]. Considering the former, treatment will be delivered in three or five fractions, considering an α/β ratio of 10 Gy, as supported by available evidence [3, 19, 20]. The choice of the optimal fractionation schedule will be made according to clinical parameters, including tumor size, location (central vs. peripheral) and preexisting patient’s comorbidities (e.g. chronic obstructive pulmonary disease, interstitial disease lung). Treatment planning will be realized with dedicated systems, namely Raystation [RaySearch Laboratories] and Precision-Cyberknife [Accuray], while treatment delivery will be performed with either TrueBeam [Varian], Tomotherapy [Elekta], or Cyberknife [Accuray]. Regarding surgery, all patients will receive anatomical pulmonary resection such as segmentectomy or lobectomy with systematic lymphadenectomy, in compliance with current clinical practice guidelines [3, 21].

### Power calculations

The main aim of the MONDRIAN study is to assess the predictive value of the multi-omic predictive score for SBRT response, with the primary outcome of interest being PFS. A sample size of 270 allows to verify whether the score (classified as low and high, based on the median value) is able to predict treatment response on PFS with 80% of power [22]. With a median progression-free survival time (MPFST) of 27 and 14 months in the SBRT and surgery groups, respectively [23], for patients with high score, the corresponding hazard ratio (HR) is 0.52. For patients with the low score, we assume a MPFSTs of 14 and 27 months in the SBRT and surgery groups, respectively, with a corresponding HR of 1.93. Under the assumption of uniform distribution for the censoring time during the study period, a two-sided 1% type I error calculation was set to account for multiple testing. Given the possibility of 10% of missing values/lost to follow-up, an approximate number of 300 patients, with a 1:2 ratio for SBRT and surgery, respectively, will be enrolled.

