## Methods/ design

### Aim and setting of the study

The primary aim of this study- named MONDRIAN (Multi-Omics Integrative Modeling for Stereotactic Body Radiotherapy in Early-stage Non-Small Cell Lung Cancer), is to identify a multi-omic biomarker of response to SBRT in ES-NSCLC. Additionally, the study aims to assess whether the combination of clinical, imaging and biologically-derived information could yield better prediction than individual-omics alone. This will be realized through a data-driven, bottom-up approach integrating prospectively collected data from the radiomic, genomic, and protein domains, to more consolidated clinical parameters, as detailed below.

MONDRIAN is designed as a monocentric, prospective observational explorative cohort trial. It is expected to enroll ES-NSCLC patients treated with either SBRT or surgery with a 1:2 ratio, respectively, for a total of 300 patients, over a 5-year timeframe. The primary endpoint is progression-free survival (PFS) defined as the time between the beginning of SBRT or the date of surgery, and any disease progression (local, regional, distant), death from any cause, or last follow-up, whichever comes first. Secondary endpoints are the investigation of prognostic factors from clinical, imaging, genomic and proteomic data, the longitudinal validation of gene expression and proteomics profiling among tissue- and liquid biopsies-derived samples, and the creation of a permanent dataset of high-quality, prospectively collected multi-dimensional data.

The whole study will be conducted at the European Institute of Oncology (Istituto Europeo di Oncologia, IEO) IRCCS, in Milan, Italy.

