### Study design

The study is divided into five main tasks, summarized in Table 1. Of note, being an observational trial, the care path will strictly adhere to best clinical practice guidelines [3], and no additional examinations will be required with the sole exception of a venous blood sampling, which will be performed at baseline and at the first disease progression or last follow-up (whichever comes first), as an optional part of the study. The aim of this sub-task is to perform a longitudinal validation of gene expression and proteomic profiling between tissue samples and liquid biopsies. Due to the experimental nature of these analyses, along with their potentially high risk/high gain profile- this sub-study is considered as a benchmark, and participation will be limited to 60 patients treated with SBRT. Participation in this sub-study will be optional, and declining will not affect enrollment in the main study.

**Table 1 Tab1:** Summary of the five tasks of the study

Task	Timeframe (months)	Task Description
Task 1- Clinical Study	1–48	Eligibility check and patient enrollment (WP1), collection of baseline patient-, disease- and treatment-related data (WP2), follow-up and collection of patient-, disease and treatment-related data (WP3)
Task 2- Imaging/Radiomic Study	1–60	Collection of qualitative and semi-quantitative CT image metrics (WP4), collection of qualitative and semi-quantitative 18FDG-PET/CT image metrics (WP5), radiomic analysis on CT and [18 F]-FDG-PET/CT images (WP6)
Task 3- Gene Expression Study	1–48	Sample collection and storage of FFPE samples from either the resected tumor or tissue biopsy (WP7), gene expression profiling through the NGS-based assay OIRRA (WP8)
Task 4- Proteomic Study	1–48	Sample collection and storage of FFPE samples from either the resected tumor or tissue biopsy (WP9), proteomics analysis through the PATH-MS method (WP10)
Task 5- Integrative Model Building	48–60	Data cleaning, exploratory data analysis, regularization (WP11), model training and validation (WP12)

**Abbreviations**: [18 F]-FDG-PET/CT: [18 F]Fluorodeoxyglucose positron emission tomography, CT: computed tomography, FFPE: formalin-fixed paraffin-embedded, OIRRA: Oncomine™ Immune Response Research Assay, PATH-MS: (PAThology tissue analysis of Histones by Mass Spectrometry, WP: work package

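### The stated 80% power is that of a score fixed in advance and tested in 270 independent patients, whereas the plan indicates that the score will be learned within the study

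*Protocol article*

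**What the plan says.** The Power calculations section of the protocol article states "A sample size of 270 allows to verify whether the score", cut at its median into a low and a high half, does what is claimed for it. The claim is that it "is able to predict treatment response on PFS with 80% of power". The assumed effect is a full crossover. In the high-score half, median PFS is 27 months with SBRT and 14 with surgery: "for patients with high score, the corresponding hazard ratio (HR) is 0.52". In the low-score half it assumes "MPFSTs of 14 and 27 months in the SBRT and surgery groups, respectively, with a corresponding HR of 1.93". Censoring is uniform over the study period, with no window given in months. On error control it says "a two-sided 1% type I error calculation was set to account for multiple testing". Allowing 10% for missing data or loss gives about 300 patients, SBRT to surgery 1:2.

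The score does not exist at the start. Aim and setting of the study makes identifying it the primary aim and adds "This will be realized through a data-driven, bottom-up approach integrating prospectively collected data". Table 1 in Study design places regularization and "model training and validation (WP12") in Task 5, months 48–60. The study is single-centre. The article names no earlier score and no other cohort, and does not say how patients are divided between training and validation.

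**The concern.** The calculation spends every evaluable patient on the test: 270/0.9 = 300, the whole enrolment. Nobody is left over for training, and the hazard ratios are entered as if the score's sorting of patients were already settled. A score learned from the study's own data has to pay somewhere. A hold-out reduces the number of test patients. Cross-fitting keeps all 270 but normally shrinks the contrast between score groups. Testing in the training patients invalidates the 1% level. The section allows for none of these, and a 1% level chosen for multiple testing does not correct for overfitting.

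This is the only operating characteristic stated for the primary aim. If true power is well below 80%, a null result says much less about a multi-omic biomarker than readers would assume. The Discussion looks ahead to intensified treatment research in high-risk patients, so a false positive would also matter.

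**Working it through.** **Inputs from Power calculations:** medians 27 and 14 months, crossed over between score halves; 270 evaluable patients; 1:2 ratio; two-sided 1% (critical value 2.576). A median split gives cells of 45 and 45 (SBRT) and 90 and 90 (surgery).

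**Assumptions added:** exponential PFS; uniform censoring over (0, T), with T = 40, 48 or 60 months. The Abstract gives 60 months for the project, Table 1 gives 48 for the clinical task, and 40 is the value that returns the stated power.

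**Formulas**
- Hazard λ = ln 2/median.
- P(event) = 1 − (1 − exp(−λT))/(λT).
- Effect = ln(27/14) − ln(14/27) = 2 × 0.657 = 1.314, a ratio of hazard ratios of 3.72.
- SE² = sum of 1/events over the four cells.
- Power = Φ(effect/SE − 2.576).

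**Step 1: reproduce the plan's figure.** The hazard ratios check: 14/27 = 0.52 and 27/14 = 1.93. For a known score in all 270:

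| T (months) | Events: SBRT high / SBRT low / surgery high / surgery low | Total | SE | Effect/SE | Power |
|---|---|---|---|---|---|
| 40 | 16.9 / 25.4 / 50.8 / 33.7 | 127 | 0.385 | 3.415 | 79.9% |
| 48 | 19.1 / 27.8 / 55.6 / 38.3 | 141 | 0.364 | 3.611 | 85.0% |
| 60 | 22.0 / 30.6 / 61.3 / 44.1 | 158 | 0.342 | 3.840 | 89.7% |

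So 80% at 270 is the power of a treatment-by-score interaction test of a known score using everyone, with a window of about 40 months.

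**Step 2: hold-out.** With a fraction f held out, effect/SE is multiplied by √f. Example, f = 0.5 and T = 60: 3.840 × 0.707 = 2.715; Φ(2.715 − 2.576) = 56%.

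| Held out for the test | T = 40 | T = 48 | T = 60 |
|---|---|---|---|
| 80% (216) | 68% | 74% | 80% |
| 50% (135) | 44% | 49% | 56% |
| 30% (81) | 24% | 27% | 32% |

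These rows assume that the learned score keeps the full contrast in the held-out patients.

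**Step 3: cross-fitting.** All 270 are scored by models that did not see them, and a fraction q of the log-HR contrast survives, so effect/SE is multiplied by q (SE held fixed). Example, q = 0.8 and T = 40: 3.415 × 0.8 = 2.732; Φ(2.732 − 2.576) = 56%.

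| Contrast kept | T = 40 | T = 60 |
|---|---|---|
| 100% | 80% | 90% |
| 90% | 69% | 81% |
| 80% | 56% | 69% |
| 70% | 43% | 54% |

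**Step 4: type I error (illustrative).** In a simulation with no true effect and a ridge-type score, testing in the training patients rejected at nominal 1% in 86% of runs with 20 candidate features and 100% with 100 or 400. Five-fold out-of-fold scores with an ordinary z test rejected in 3.5–5.3% of 400 runs, so even a cross-fitted score may need a resampling p-value. The learner and feature counts are assumptions, since the article gives none. These results show direction, not the trial's error rate.

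**The case against.** The strongest reply is that the article never says where or how the score is validated. Table 1 only lists training and validation as a work package, and the full protocol may specify a scheme. This stands: use of the same patients is inferred from the single-centre design and the absence of any other cohort. A reader might infer that the plan tests the score in its own training data and so all but guarantees a false positive. The documents do not support that, since no such analysis is described and regularization and validation are listed.

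Second, the hazard ratios of 0.52 and 1.93 may be meant as the effect of the score as finally delivered, out of sample. Under cross-fitting the 80% would then survive, and discounting the contrast again would count the loss twice. This is possible, but the text does not say so. Hence the stronger reading, that the design certainly lacks 80% power, is not proven.

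Third, 270 has some slack if the window is 60 months: 216 test patients still give 80%. That leaves 54 for training, about 18 of them SBRT at the 1:2 ratio, which is very few for a radiomic, genomic and proteomic score. At 48 months the same split gives 74%.

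Fourth, the study calls itself explorative. That softens the consequences, but the section still attaches a confirmatory power and error level to the score.

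**Conclusion.** The concern holds in this form: the 80% is stated without the condition on which it depends, namely a locked score in 270 patients not used to build it (or hazard ratios that are explicitly out-of-sample effects). The rest of the article indicates a score learned within the study. The arithmetic of the 80% is not itself at fault, since it reproduces with a window of about 40 months.

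The size cannot be fixed from the article. For windows of about 40 to 60 months it is 44–56% with a 50% hold-out and 24–32% with a 30% hold-out. With all 270 scored out of fold it is 69–81%, 56–69% or 43–54% if 90%, 80% or 70% of the contrast is kept. The splits, the retained fractions and the censoring window are assumptions. The medians, ratio, level and sample size are the plan's.

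**What to change.** In Power calculations:

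1. State that the 80% applies only to a locked score tested in independent patients, or state explicitly that the hazard ratios are out-of-sample effects and why they are plausible as such.
2. Replace the 80% with the power of the actual training and validation scheme, simulated under stated assumptions (censoring window, number of features, learner, strength of signal).
3. Base the primary treatment-by-score test only on out-of-sample scores: either cross-fitted with all model building (feature selection, tuning, median cut) inside the folds, or from a hold-out of stated size.
4. Assess type I error over the whole pipeline by resampling, and say what is resampled. The scheme must respect the propensity score adjustment described in the Discussion: freely permuting treatment breaks its link with the confounders, and permuting outcomes tests a complete null rather than the absence of interaction.

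The cost is a simulation, revised wording and probably a less favourable stated power. Enrolment and procedures do not change. Extra patients would come into question only if the investigators wished to keep 270 test patients alongside a hold-out: a 50:50 split would need 270/0.5 = 540 evaluable, or 540/0.9 = 600 enrolled. Model building is scheduled from month 48, so the change should be made before outcomes are analysed.

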### Ethical considerations, funding and registration

The study will comply with the Declaration of Helsinki and with the principles enunciated by the International Conference on Harmonization and Good Clinical Practice in May 1996 [24, 25]. Signature of the general written informed consent for study participation will be required to all participants. An additional written informed consent will be provided to SBRT candidates in case they are willing to be enrolled in the sub-study for the longitudinal validation of non-invasive genomic and proteomic signatures, as detailed above.

The MONDRIAN trial is supported by a research grant from the Italian Association for Cancer Research (Associazione Italiana per la Ricerca sul Cancro, AIRC)- Next Generation Clinician Scientist- Call 2022 (ID: 28,282).

The study has been approved by the Institutional Ethical Committee (ID number: IEO 1973- UID3940), and then registered at clinicaltrials.gov (NCT05974475).

## Discussion

The rationale of the MONDRIAN study fits into the early stages of applying the omics sciences to Radiation Oncology, and into the wider concepts of personalized medicine. These principles are applied to the largely uninvestigated setting of ES-NSCLC, with the primary aim of investigating factors associated with radiosensitive and radioresistant phenotypes. In addition to seeking a mechanistic understanding of the disease, the study aspires to uncover clinically actionable insights by the identification of different risk profiles for disease progression. Arguably, this would set a benchmark for further investigations on treatment intensification strategies for high-risk patients, which may include dose escalation and/or combination therapies (e.g. immunotherapy).

Several risk mitigation strategies have been developed to ensure sufficient enrollment, accurate prospective collection of reliable data, and- overall- successful study completion. Of these, it is important to underline that interdependence among tasks will be significantly diminished thanks to the training of single- and dual-omics models, in addition to the multi-omic model. This strategy serves two purposes: on the one hand, it minimizes the weight of potentially uninformative data, on the other, it allows to explore how the combination of omic-features contributes to the predictive performance of models.

Another potentially relevant issue may involve negative patient selection in the SBRT cohort. Indeed, SBRT is often regarded as the second-choice curative treatment for ES-NSCLC, particularly in case of contraindications to anesthesia and/or surgery. Consequently, a certain degree of selection bias is anticipated, also due to the non-randomized nature of the MONDRIAN study. Hence, all models will be adjusted using a propensity score, which will be calculated for each patient by combining the beta coefficients of the clinical variables included in a logistic regression model where the treatment (SBRT vs. surgery) serves as the outcome. This adjustment aims to minimize the impact of potential confounders and ensure a reasonable level of comparability between treatment groups. A propensity score approach based on patient matching will also be employed and compared with the method relying on propensity score adjustment.

To the best of our knowledge, this is the first study to investigate predictors of response to SBRT in ES-NSCLC through the integration of data from multiple -omic disciplines. This would provide an unprecedented opportunity to characterize the disease, and to elucidate the interaction between determinants of radiosensitivity and radioresistance. The focus on potentially actionable targets is timely in the wider context of high-precision RT, RT/systemic therapy combinations, and personalized medicine.

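### A treatment propensity score applied to every model is the wrong adjustment for the prognostic-factor models: a clinical factor that is part of the score is adjusted for a quantity containing itself

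*Protocol article*

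**What the plan says.** The Discussion raises selection bias in the SBRT cohort and answers it with one general rule: "all models will be adjusted using a propensity score, which will be calculated for each patient by combining the beta coefficients of the clinical variables". The coefficients are those of a logistic model whose dependent variable is the treatment received. The stated purpose is narrower than the stated scope: "This adjustment aims to minimize the impact of potential confounders and ensure a reasonable level of comparability between treatment groups". A second method follows: "A propensity score approach based on patient matching will also be employed and compared with the method relying on propensity score adjustment".

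The models mentioned shortly before the rule come from the "training of single- and dual-omics models, in addition to the multi-omic model".

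The section on aim and setting takes PFS as the primary endpoint and adds: "Secondary endpoints are the investigation of prognostic factors from clinical, imaging, genomic and proteomic data". It also describes "integrating prospectively collected data from the radiomic, genomic, and protein domains, to more consolidated clinical parameters". The article exempts no model from the propensity rule, does not list the variables in the propensity score, and does not say whether clinical covariates are also entered directly.

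**The concern.** A treatment propensity score makes SBRT and surgery patients comparable on the variables it contains. A prognostic-factor model asks something else: how PFS differs across levels of a clinical or omic factor. Balance between treatments does not give balance across levels of that factor.

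Two consequences need to be kept apart.

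- **Clinical factors that are in the propensity score.** The factor is examined while holding fixed a sum that already includes it. Its coefficient then mixes prognosis with treatment selection.
- **Omic features.** The propensity score weights clinical variables by how well they predict treatment. A variable that matters for PFS but hardly influences the tumour board gets little weight, so the score controls it poorly.

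At stake is the secondary endpoint. A real clinical prognostic factor could be reported as null or with the wrong sign. If nothing else were adjusted for, an omic feature that merely tracks stage could be reported as prognostic.

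**Working it through.** The plan gives no figure on this point, so there is nothing to reproduce. The check is algebra, followed by simulation with assumed coefficients.

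**1. One factor entered with the propensity score.** Let two clinical variables make up the score, PS = b1·X1 + b2·X2, and let the true log hazard be t1·X1 + t2·X2. Substituting X2 = (PS − b1·X1)/b2 gives

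log hazard = (t1 − t2·b1/b2)·X1 + (t2/b2)·PS.

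The coefficient of X1 is t1 − t2·b1/b2, not t1. It is zero when prognostic effects are proportional to treatment-selection effects (t1/b1 = t2/b2). With b1/b2 positive, it falls below zero when t2·b1/b2 exceeds t1. It equals t1 if X2 has no effect on PFS.

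**2. All variables entered with the propensity score.** If the propensity score is the linear predictor, it is an exact sum of columns already in the model. With three clinical variables, treatment and the score, the matrix has 5 columns and rank 4.

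**3. Size under assumed values.** Assumptions, none of them from the document except the 300 patients:
- age, stage and lung function are independent standard normal variables;
- log-odds for SBRT are 0.8 for age, −0.8 for lung function, and 0, 0.3 or 0.8 for stage (call this bs);
- PFS log HRs per SD are 0.30 for age and ln 2 = 0.693 for stage, and treatment has no effect;
- censoring is uniform over 0–60 months, with 300 replicates per setting.

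An approximate prediction for age comes from projecting stage on what remains of the propensity score once age is fixed: 0.30 − 0.8 × 0.693 × bs/(bs² + 0.8²).
- bs = 0: 0.30.
- bs = 0.3: 0.30 − 0.554 × 0.3/0.73 = 0.07.
- bs = 0.8: 0.30 − 0.554 × 0.8/1.28 = −0.05.

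| Cox model with treatment, mean log HR | bs = 0 | bs = 0.3 | bs = 0.8 |
|---|---|---|---|
| Age, with propensity score (true 0.30) | 0.26 | 0.06 | −0.05 |
| Age, with stage and lung function entered directly | 0.31 | 0.31 | 0.31 |
| Stage, with propensity score (true 0.69) | 0.69 | 0.62 | 0.54 |

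The simulation agrees with the approximation. The shortfall at bs = 0 (0.26 against 0.30) is the usual attenuation in a Cox model that omits a strong covariate.

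**4. Omic feature with no effect of its own, correlated 0.5 with stage, same runs.**

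| Mean log HR (share significant at 5%) | bs = 0 | bs = 0.3 | bs = 0.8 |
|---|---|---|---|
| No clinical adjustment | 0.30 (96%) | 0.28 (97%) | 0.27 (93%) |
| Propensity score only | 0.30 (97%) | 0.26 (90%) | 0.18 (59%) |
| Clinical covariates directly | 0.00 (7%) | 0.00 (4%) | −0.01 (3%) |

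The propensity score does not create this confounding. It leaves it in place when stage hardly drives treatment, and removes part of it when stage drives treatment strongly.

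**5. The purpose for which the propensity score is meant.** In the same runs the true treatment effect was 0. The unadjusted log HR for treatment was 0.17, 0.28 and 0.43. With the propensity score it was between −0.001 and 0.012. For the treatment contrast the rule works.

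**The case against.** **Scope.** The rule sits in a paragraph about selection into SBRT, its purpose is comparability of the treatment groups, and it never mentions the secondary endpoint. It may have been meant only for models containing a treatment contrast. That is a plausible intention, but the wording has no such limit, and the models discussed just before it are those in which omic features are assessed. The text should state the limit if it is intended.

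**Form of the score.** The article could mean the fitted probability rather than the linear predictor. Exact collinearity then disappears, but the distortion does not. In a separate simulation (270 patients, a clinical factor with true log HR 0.40), adjusting for the fitted probability gave 0.05 and −0.04 under two assumed patterns of effects. Exact collinearity is also a visible redundancy: dropping the propensity score returns the directly adjusted model. Dropping a clinical variable instead leads back to step 1.

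**Stronger readings.** A reader might infer that every clinical factor is adjusted for itself. The document does not support this, because it does not list the variables in the propensity score; the point holds for those included. A reader might also infer that omic features will be left confounded by stage or size. That needs the propensity score to be the only clinical adjustment. The article does not say so, and its plan to integrate omic data with clinical parameters leaves room for direct entry. Covariate lists are commonly left to the full protocol or SAP, so their absence is no fault here.

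**Size.** Loss or reversal of a real effect is not inevitable. In the separate simulation, a factor that was the only prognostic variable kept a sound estimate (0.39) but lost power: it was detected at the 1% level in 56% of runs, against 88–93% with direct adjustment across the patterns tried. The article also foresees regularised models, whereas these simulations were unpenalised.

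**Conclusion.** The point holds in limited form. As written, the rule extends a treatment propensity score to models for which it is not suited. For clinical factors in the propensity score, the algebra shows a coefficient that depends on treatment selection and may be attenuated or reversed. How far depends on coefficients the document does not give; the figures of 0.26, 0.06 and −0.05 for a true 0.30 illustrate a range and do not predict this study's results. Exact collinearity requires the linear-predictor form with all its variables also entered. The omic limb is conditional on there being no other clinical adjustment.

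The SBRT-surgery contrast and the test of the multi-omic score by treatment on PFS are not affected. Because a secondary endpoint of an explorative study is at stake, severity is moderate.

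**What to change.** State that propensity adjustment and matching apply only to models that estimate a treatment effect or a treatment-by-score effect.

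For the prognostic-factor models, remove the propensity score. Include treatment as a stratum or a covariate, and enter directly the baseline clinical covariates that the Study design section already says will be collected: for example stage, lesion location, demographics, performance status, Charlson index and spirometry. Penalise them if there are many relative to the number of events. Tumour size and histology could be added if recorded; the article mentions them for choice of fractionation and for eligibility, but does not name them among the collected variables.

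The cost is a few degrees of freedom and a little more analysis work. No new data are needed, and the change should be made before model building starts in month 48.
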